#### **2.2.2 Secondary Objectives**

- Compare safety of topical vs. injectable anesthesia for local anesthesia during Shang Ring circumcision
- Compare ease of use of topical vs. injectable anesthesia for local anesthesia during Shang Ring circumcision
- Explore service optimization for use of topical anesthesia in conjunction with Shang Ring circumcision
- Compare duration of post-procedural analgesic effects between the topical vs. injectable anesthesia groups
- Compare satisfaction with the topical vs. injectable anesthetic among study participants

- Compare satisfaction with the topical vs. injectable anesthetic among circumcision providers

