### 3.2.2 Secondary Endpoints

- To compare safety of the two anesthetic techniques we will document rates of moderate and severe AEs, device-related malfunctions, occurrence of device displacement, and time to complete clinical wound healing
- To compare ease of use of the topical vs. standard injection technique for local anesthesia during Shang Ring circumcision, we will document dwell time required for onset of adequate anesthesia with the topical cream and time to adequate anesthesia with injectable anesthesia, potency of anesthesia provided by both techniques, and problems encountered during anesthesia with the two techniques.
- We will also explore service optimization in terms of determining how to best sequence and group patients for Shang Ring circumcision given the dwell time necessary for topical anesthetic effect.
- To compare duration of post-procedural analgesic effects between the topical vs. injectable anesthesia groups, we will document reported pain at various time points such as 1 and 24 hours post-circumcision between the two groups using the VAS.
- To compare satisfaction with topical vs. injectable anesthetic, we will interview study participants and their parents or legally acceptable representative (LAR) as appropriate to document acceptability and satisfaction with the circumcision, the Shang Ring procedure, post-procedure pain, and time to return to normal activity between the two techniques
- To compare satisfaction with the topical vs. injectable anesthetic among clinical providers in the study, we will interview them about their experiences, acceptability and satisfaction with the two anesthetic techniques

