### Phase II

| STUDY ACTIVITY                         | Day 0 Visit | Day 7 Visit | Day 42 Visit |
|----------------------------------------|-------------|-------------|--------------|
| Informed Consent Process               | X           |             |              |
| Assign Participant Number              | X           |             |              |
| Physical Exam and Medical History      | X           |             |              |
| Genital Exam                           | X           | X           | X            |
| Screening Checklist                    | X           |             |              |
| Demographic Survey                     | X           |             |              |
| Obtain Locator Information             | X           |             |              |
| Randomization                          | X           |             |              |
| Circumcision Procedure                 | X           |             |              |
| Shang Ring Device Removal              |             | X           |              |
| Assess Pain and/or AEs or SAEs         | X           | X           | X            |
| If permitted take Penile Photograph    | X           | X           | X            |
| Review Concomitant Medications         | X           | X           | X            |
| Schedule Follow-Up Visit               | X           | X           |              |
| Schedule follow-up if wound not healed |             |             | X            |
| Reimburse Participant                  |             | X           | X            |
| Final Status Form                      |             |             | X            |

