All other endpoints will be summarized by anesthetic technique and compared between groups using either two-sample t-tests or chi-squared tests, as appropriate for the endpoint, all conducted at the two-sided 0.05 significance level. We will not make any adjustments for multiple comparisons. 95% confidence intervals for differences between groups will be presented. Missing data will be assumed to be missing in random fashion and ignored.

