| Mild AEs                                                                                                  | 43     | 2.2% (1.6%, 2.9%) |
| Anesthetic complication                                                                                   | 1      |                   |
| Pain during placement                                                                                     | 13     |                   |
| Edema                                                                                                     | 3      |                   |
| Injury                                                                                                    | 3      |                   |
| Partial detachment                                                                                        | 3      |                   |
| Bleeding                                                                                                  | 2      |                   |
| Wound disruption                                                                                          | 15     |                   |
| Insufficient skin removed                                                                                 | 3      |                   |

Adapted from WHO Technical Advisory Group on Innovations in Male Circumcision: Evaluation of Two Adult Devices. Meeting report: Published in August 2013. Geneva, Switzerland. ISBN 978 92 4 150563 5.

The figures in the above table are for Shang Ring circumcision in adults. In a study in China which involved 824 children the complication included infection (0.4%), edema (3.2%), and insufficient skin removal (0.9%). Average time for wound healing was 13.4 ± 5.8 days after circumcision (Yan, 2010). We found low rates AEs in our recently completed study of use of the Shang Ring in children in Kenya; among the 80 boys under 18 years of age who participated in the study there were no severe AEs and four moderate AEs (three cases of wound disruption, all which healed with conservative management, as well as one case of postoperative pain requiring further analgesics).

During the follow up visits, study staff will assess and provide follow-up care and/or referrals for any post-operative complications. If complications or delayed healing require longer follow-up, men will be followed by study staff as long as necessary.

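### Phase II sets an objective on duration of analgesia but measures only pain intensity at example time points, and gives analgesic use no role in the analysis

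*Combined protocol and SAP*

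**What the plan says.** Section 2.2.2 lists as a Phase II secondary objective: "Compare duration of post-procedural analgesic effects between the topical vs. injectable anesthesia groups". Section 3.2.2 gives it one endpoint: "we will document reported pain at various time points such as 1 and 24 hours post-circumcision between the two groups using the VAS". The hours are examples, so the time points are not fixed.

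Section 9.2 covers every non-primary Phase II endpoint with one sentence: "All other endpoints will be summarized by anesthetic technique and compared between groups using either two-sample t-tests or chi-squared tests", "all conducted at the two-sided 0.05 significance level", with 95% confidence intervals for the differences. A VAS score treated as a number falls under the t-test. On incomplete data, 9.2 adds: "Missing data will be assumed to be missing in random fashion and ignored".

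The Phase II table in section 8.5 has the row "Review Concomitant Medications" at days 0, 7 and 42, and section 13.1 also lists this information for all visits. Section 9.2 gives it no use. No section makes analgesic use an endpoint or says how to treat a pain score taken after a dose. Section 12.3.1 reports, from the group's earlier study of 80 boys, "one case of postoperative pain requiring further analgesics".

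Section 8.3 schedules Phase II follow-up on days 7 and 42 only. The documents do not say how the 24-hour score is obtained.

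**The concern.** There are two linked problems.

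1. **The endpoint does not match the objective.** Duration is a time. Pain scores at two clock times show how much pain there was at those times. This holds whatever analgesics are taken.
2. **Analgesic use is not handled.** A participant whose anesthetic wears off early has more reason to take an analgesic, and his later score may then be low because of the dose. If the arm with the earlier offset takes more, the later VAS difference is pulled towards zero.

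At stake is one of the comparisons that bears on whether topical anesthesia can replace injection: what participants go through once the anesthetic wears off. As planned, the trial could report similar scores at 24 hours without being able to say whether the effects lasted equally long.

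**Working it through.** **Why two readings do not give a duration.** Take one effect that ends at 2 hours and another that ends at 20 hours. At 1 hour both are present, and at 24 hours both are gone. The pattern is the same although the durations differ by 18 hours.

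**Inputs from section 9.1.** SD 1.8, difference of 1 on the 0 to 10 scale, two-sided 0.05, 345 randomised 2:1 (230 v 115), at least 300 with complete follow-up (200 v 100). The plan's calculation is for its pain-score comparison; it is used here as a yardstick for the later scores.

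**The plan's own figure.** SE = SD × √(1/n₁ + 1/n₂), and power ≈ Φ(difference/SE − 1.96).
- 230 v 115: SE = 1.8 × √(1/230 + 1/115) = 0.2056, power 99.8%.
- 200 v 100: SE = 1.8 × √(1/200 + 1/100) = 0.2205, power 99.5%.

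Both agree, after rounding, with the stated 100%.

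**Attenuation.** The documents give neither use by arm nor relief per user, so both are assumptions. Difference seen = 1 − (excess proportion using analgesics in the arm with the earlier offset) × (relief in VAS points). With 200 v 100 and a relief of 2 points:

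| Imbalance in use | Hidden | Seen | Power |
|---|---|---|---|
| 0 points | 0 | 1.0 | 99.5% |
| 10 points | 0.2 | 0.8 | 95% |
| 25 points | 0.5 | 0.5 | 62% |
| 40 points | 0.8 | 0.2 | 15% |

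The relief assumption matters. At a 20-point imbalance, relief of 1, 2 or 3 points leaves 0.8, 0.6 or 0.4 (power 95%, 78%, 44%). At 40 points it leaves 0.6, 0.2 or −0.2 (78%, 15%, 15%, the last in the wrong direction).

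**How large an imbalance is plausible.** Suppose use is triggered by one common pain threshold, scores are normal with SD 1.8, and the untreated difference is 1 point. The largest possible imbalance is then 2Φ(0.5/1.8) − 1 = 22 percentage points. At 2-point relief this leaves 1 − 0.22 × 2 = 0.56, with about 72% power at an unchanged SD. An imbalance of 40 points needs more than this, such as a larger pain gap at an earlier hour or different thresholds by arm.

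Trials were also simulated with pain-triggered use: 200 v 100, scores limited to 0–10, threshold 4 or 5, relief 1 to 3 points, half or all of those above the threshold taking a dose. A true difference of about 0.97 shrank to between 0.34 and 0.89, and power was 74% to 99%. Power falls less than in the fixed-SD table because relief given to those in most pain also narrows the spread of scores.

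**Feasibility of a time-to-event analysis.** With 2:1 allocation, two-sided 0.05 and 80% power, the log-rank test needs (1.96 + 0.8416)² / [(2/3)(1/3)(ln HR)²] events: 215 for a hazard ratio of 1.5, 113 for 1.75 and 74 for 2. These are 72%, 38% and 25% of 300 participants. The hazard ratios are assumed.

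**The case against.** The strongest reply is that the bias from analgesics is unproven. The documents give no regimen, use rate or relief figure. The only direct sign of use is a single case among 80 boys, reported as an adverse event. Equal use gives no bias, and under simple pain-triggered use the attenuation is partial. All of that stands.

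A reader might infer that the plan will hide a shorter-lasting anesthetic, or that the trial would declare the durations equal. The documents do not support either reading. The outcome depends on unknown use by arm, and section 9.2 plans two-sided difference tests with confidence intervals, not a claim of equivalence. Nor does the plan say that analgesics will be disregarded. It is silent.

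VAS scores regardless of analgesic use are also a legitimate measure of the pain participants experienced, so they should be kept. They answer a different question from duration.

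Section 9.2 is a summary, and a detailed analysis plan is promised. That could settle the handling of scores, but nothing says it will. It need only be approved before analysis starts, and a dose time not recorded at the time cannot be recovered reliably afterwards. The eCRFs are not in the documents, so dose time may already be a field. If so, only the analysis needs to change.

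Finally, if all participants receive analgesics routinely, time to first dose reflects dispensing and not wearing-off. This is a valid limit on the remedy, and the definition below allows for it.

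**Conclusion.** The mismatch is certain on the text: the objective is duration, and the only endpoint is pain intensity at time points given as examples. It needs no assumption about analgesics.

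The attenuation is conditional. It goes towards zero if the arm with the earlier offset takes more analgesic, and its size cannot be derived from the documents. The illustrations (0.8, 0.5 or 0.2 points seen out of 1) rest on an assumed 2-point relief, assumed imbalances and the plan's SD of 1.8. Partial attenuation is the more likely case; near-complete masking needs a large imbalance or strong relief.

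This concerns one Phase II secondary endpoint. The primary endpoint, maximum pain during the procedure reported straight after it, is unaffected. The change should be made before Phase II enrolment, because it depends on data captured at the time.

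**What to change.** **In section 9.2**, analyse duration by randomised arm:
- Time from end of procedure to first analgesic dose, or to the first dose beyond any analgesic given routinely to all, with Kaplan–Meier curves and a log-rank test.
- The proportion using such analgesics by 24 hours, with a 95% confidence interval for the difference.
- VAS at 1 and 24 hours as a measure of experienced pain, with scores taken after analgesic use flagged.

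The randomised arm should be named because section 8.2 gives injectable anesthesia to topical participants who are not numb, and the as-treated rule in 9.2 does not say where someone given both belongs.

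**In section 3.2.2**, fix the VAS time points. State how the 24-hour score and analgesic use are obtained, for example by the phone contact that section 8.2 already uses for reminders. Recall at day 7, partly by boys aged 10 to 15 or their parents, would be unreliable.

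**On the concomitant medication eCRF**, record the date and time of the first such dose, if not already captured.

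**Cost.** One field, one defined contact and two analyses, with no extra visit and no change to treatment. The main downside is that dose time is reported by the participant or parent.

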## 4.0 STUDY DESIGN

The study, to be conducted in two phases, will examine procedural and clinical outcomes, as well as participant and provider acceptability, of adaptations of the Shang Ring technique for male circumcision that would simplify its use and increase its acceptability.

- Phase I will be non-comparative for exploration of the no-flip technique for Shang Ring circumcision (i.e. all participants will be circumcised using the no-flip Shang Ring technique). Historical data from standard Shang Ring circumcisions conducted in Africa (Kenya, Uganda and Zambia) will be used as the comparison group. Men will be randomized to removal at 7 days after circumcision vs. delayed removal, to assess occurrence and safety of spontaneous detachments following circumcision with the no-flip technique.
- Phase II will compare the use of topical vs. injectable anesthesia for Shang Ring circumcision. Participants will be randomized to topical vs. injectable anesthesia in a 2:1 ratio. We rationalize the 2:1 randomization scheme given that we will have just completed Phase I in which 200 men and boys will have been circumcised using the no-flip technique with injected anesthesia. However, given the subjectivity associated with using reported pain as the primary endpoint, we believe it is critical to randomize participants in this phase of the study.

Because of the possibility that boys and men could have different outcomes after no-flip Shang Ring circumcision or could respond differently to use of topical anesthesia, we

will recruit participants equally in two age groups in both phases; 50% of participants recruited in each phase will be between 10-15 years old and the other 50% over 15 years old. Because recruitment shall be taking place at two sites, which may have different recruitment rates, and because clients need to be randomized 1:1 and 2:1 into the Phase 1 and Phase 2 treatment groups, respectively, appropriate stratified block randomization techniques by age will be applied to achieve the intended number of participants per treatment group.

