## 5.0 STUDY SITES

This study will be conducted at two primary sites in Kenya: (1) Homa Bay County Hospital, Homa Bay County, in the western region, and (2) Vipingo Health Center, in Kilifi County, along the coast. The study sites were determined in conjunction with NASCOP VMMC National coordinator and county health authorities. Circumcisions will be done by trained medical officers, clinical officers or nurses.

Staff at the Homa Bay County Hospital have had extensive experience with use of the Shang Ring in adults, having been the site where the previous four Shang Ring studies with adults described earlier were conducted. They also have experience with Shang Ring circumcisions in boys under 18 years old as the county hospital was the site for the Shang Ring in children pilot study described above.

Staff from the site in Vipingo conduct conventional surgical circumcisions in men and boys but do not currently have experience with the Shang Ring. Clinical officers and nurses from the site will be trained on the Shang Ring procedures by staff from Homa Bay prior to study enrollment. The staff from Homa Bay have experience training other male circumcision providers on use of the Shang Ring, having previously trained providers from other facilities in Kenya, as well as from Uganda and Zambia.

Due to the volume of men that we plan to recruit in a relatively short time period, each primary site may use outreach services or additional clinics to recruit and circumcise study participants similar to what we did in the Shang Ring Demonstration Study conducted in 2012 in Homa Bay (KEMRI NON-SSC protocol # 299) where we involved five satellite sites and incorporated outreach activities within Homa Bay district.

The priority sub-counties for additional recruitment within Homa Bay County will be selected with guidance from County Health Management Team. This will similarly be how priority sub-counties would be selected around our Vipingo site. Previously, within Homa Bay county, Ndiru and Nyangoro Health Centres participated in the Demonstration Study and still have staff that were previously trained on Shang Ring VMMC technique.

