### **Phase II**

Assuming positive outcomes of Phase I, we will use the no-flip technique for all Shang Ring circumcisions in Phase II.iv In this phase, participants will be randomized to topical or injectable anesthesia in a 2:1 ratio. We rationalize the 2:1 randomization scheme given that we will have just completed Phase I in which 230 men and boys will have been circumcised using the no-flip technique with injected anesthesia. However, given the subjectivity associated with using reported pain as the primary endpoint, we believe it is critical to randomize participants in this phase of the study. Because of the possibility that boys and men could respond differently to use of topical anesthesia we will recruit participants equally in two age groups; 50% ages 10-15 years old and 50% those over 15 years old.

To get a better sense of minimum dwell time necessary for adequate anesthesia, we will test for anesthetic effect more frequently (e.g. every 3-5 minutes) in the first 10 participants randomized to the topical arm in each age group (10-15 and over 15 years old), as well as any participants randomized to the injectable arm during this period. During this time we will also closely monitor the occurrence of any significant problems with application of the topical anesthesia or potency of the anesthesia with the topical agent. This will allow us to establish a minimum dwell time which will be important for logistic and program planning purposes, although each participant will be tested for numbness as described below before the circumcision procedure is started. Given the previous experience with use of EMLA cream for male circumcision, we are expecting that it will provide adequate anesthesia for Shang Ring circumcision. Should we determine that in fact it does not, or that there are unexpected problems, we may explore other options such as 4% or 5% lidocaine cream.

---

iv Given the experience with the no-flip technique in China and our experience with the technique in the pilot study on use of the Shang Ring in children in Kenya, we are not expecting any outcomes that might suggest that the no-flip technique is inappropriate, however, should that be the case, we will use the standard Shang Ring technique for circumcisions in Phase II.

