## 9.0 STATISTICAL CONSIDERATIONS

### 9.1 Study Size Justification

By recruiting 230 participants into Phase I of the study we expect to have complete follow-up data on at least 200. This sample size number is in line with the recommendations from the World Health Organization for clinical evaluation of MC devices, which is based on an ability to rule out an AE rate of about 5% with a new use of a device that has already been shown to be safe in a larger group of men in RCTs and demonstration studies. (WHO 2012)

In Phase II, by recruiting 345 participants, we expect to have complete follow-up data on at least 300. For comparing postoperative pain scores, we will randomize 345 males in 2:1 ratio to topical vs. injectable anesthesia for circumcision. This sample would provide 100% power to detect a mean difference of 1 on the 0 to 10 pain scale using a 2-sided test at the 0.05 significance level. This calculation assumes a standard deviation of 1.8, which is based on prior data. For other binary endpoints, this sample size will provide at least 80% power to detect absolute differences in proportions between groups of at least 20% separately within each site using two-sided tests at the 0.05 significance level. We will not make any adjustments for multiple comparisons between randomized groups.

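### Randomisation is stratified by age group, but section 9.2 names no analysis adjusted for age and plans no result by age group

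*Combined protocol and SAP*

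**What the plan says.** Section 4.0 recruits half of each phase at ages 10-15 and half over 15. It says that "appropriate stratified block randomization techniques by age will be applied to achieve the intended number of participants per treatment group". The same sentence mentions the two sites and their possibly different recruitment rates as part of the reason, but age is the only stratum it names. Section 8.2 (Phase II) gives the purpose of the age groups: "Because of the possibility that boys and men could respond differently to use of topical anesthesia".

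Section 9.2 is headed as a summary. It says that a detailed analysis plan will follow and that departures from the summary will be documented there. For Phase II it says three things:

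- VAS pain is compared between randomisation groups. No test or model is named.
- Adverse events are tabulated by group, pooled and within each site.
- All other endpoints are "compared between groups using either two-sample t-tests or chi-squared tests, as appropriate for the endpoint".

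Phase I adverse events are tabulated overall and by site. No age term, result by age group or arm-by-age estimate appears anywhere in 9.2. Section 9.3 times the Phase II interim analysis by the number treated in each age group, but describes the data for the DSMB as split by treatment group.

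**The concern.** Age determines recruitment, the block lists and the timing of the Phase II interim analysis, and then has no role in the analysis. Two things follow.

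1. **Precision.** Stratified allocation removes chance imbalance in age between the arms, so the arm difference varies less from trial to trial. A plain two-sample test does not use this. It counts the difference between boys and men as noise and reports a standard error that is too large whenever age predicts the outcome.

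2. **Interpretation.** The plan allows that boys and men may respond differently, but a single pooled difference cannot show whether they did. If topical anaesthesia worked less well in one age group only, the pooled figure would report about half of the deficit and would not show where it lay.

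**Working it through.** **Inputs from section 9.1.** N = 345, allocated 2:1 (230 topical, 115 injectable), at least 300 with complete follow-up, test "using a 2-sided test at the 0.05 significance level". The calculation "assumes a standard deviation of 1.8, which is based on prior data". Section 4.0 gives equal age groups, so each has about 172.5 participants (115 topical, 57.5 injectable). The documents give no difference in mean pain between boys and men, so the gap D is assumed and varied from 0 to 2 points.

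**Step 1: the plan's own figure.** The plan states: "This sample would provide 100% power to detect a mean difference of 1 on the 0 to 10 pain scale".
- SE = 1.8 × √(1/115 + 1/230) = 0.206; power = Φ(1/0.206 − 1.96) = 99.8%.
- With 300 completers (100 v 200), SE = 0.220 and power = 99.5%.
- The stated 100% is reproduced, allowing for rounding.

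**Step 2: effect of ignoring age.** With two equal strata, exact 2:1 allocation in each and total SD 1.8, age accounts for (D/2)² of the variance 1.8² = 3.24.
- Ratio of reported to true SE = 1/√(1 − (D/2)²/3.24).
- Actual type I error = 2 × [1 − Φ(1.96 × ratio)].

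| Assumed age gap D | SE ratio | Type I error, formula | Type I error, simulated (40,000 null trials) |
|---|---|---|---|
| 0 | 1.00 | 5.0% | 5.1% |
| 0.5 | 1.01 | 4.8% | 4.7% |
| 1 | 1.04 | 4.1% | 4.4% |
| 1.5 | 1.10 | 3.1% | 3.1% |
| 2 | 1.20 | 1.8% | 1.9% |

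The age-adjusted analysis stayed at 4.9% to 5.3% in the same simulations.

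The plan does not say whether 1.8 is the SD overall or within an age group. If it is the SD within an age group, the ratio is √(1 + (D/2)²/3.24). This gives 1.04, 1.08 and 1.14 at D = 1, 1.5 and 2, and type I error of about 4.2%, 3.4% and 2.5%.

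**Step 3: power at the design effect.** The least favourable case above is SD 1.8 within age groups and D = 2.
- Total SD = √(3.24 + 1) = 2.06; reported SE = 2.06 × 0.1142 = 0.235; true SE = 0.206.
- Power for 1 point = Φ((1 − 1.96 × 0.235)/0.206) = 99.6%.

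The loss matters only for smaller effects. For 0.6 points with total SD 1.8, simulated power unadjusted v adjusted was 84% v 86% at D = 1 and 87% v 94% at D = 2.

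**Step 4: averaging across age groups.** An effect of 1 point in one group and none in the other gives an expected pooled difference of (1 + 0)/2 = 0.5. Effects of +1 and −1 give 0.

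**Step 5: what results by age can deliver.**
- Within one age group: SE = 1.8 × √(1/57.5 + 1/115) = 0.291; 95% CI half-width = 1.96 × 0.291 = 0.57; power for 1 point = Φ(1/0.291 − 1.96) = 93% (89% with 300 completers).
- Interaction (difference between the two age-specific effects): SE = √2 × 0.291 = 0.411; half-width 0.81; power for a 1-point difference = Φ(1/0.411 − 1.96) = 68% (62% with 300). Power of 80% needs a difference of about 1.15 points (1.24 with 300).

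**Step 6: Phase I.** Section 4.0 uses historical standard Shang Ring data from Africa as the comparison. The combined adverse-event summary in section 12.3.1 (Table 2) covers adults, whereas half of Phase I will be aged 10-15. A pooled Phase I rate is therefore not like-for-like with that summary.

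**The case against.** The case against has several parts, and most of them limit the point.

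- **A reader might infer that the standard errors are invalid or that false positives rise.** They do not when arms are compared as randomised. The error is always towards a standard error that is too large, and it vanishes if age does not predict the outcome. Section 9.2 does make the as-treated comparison primary, and section 8.2 moves topical failures to injection. Age balance between as-treated groups is then not guaranteed. An age term would remove the age part of any imbalance but not the selection by failure, which is a separate matter.
- **A reader might extend the argument to site,** because one site is experienced and, in section 5.0, "Staff from the site in Vipingo conduct conventional surgical circumcisions in men and boys but do not currently have experience with the Shang Ring". That does not follow. An unadjusted test loses its nominal size only for factors that the allocation balances. With age-stratified blocks and unstratified site, simulated type I error stayed near 5% (4.7% to 5.4%) for assumed site gaps of 1 and 2 points. Adjusting for site could add precision but corrects no error.
- **A reader might conclude that site was deliberately left out of the randomisation.** Section 4.0 is unclear on this: it cites the sites as a reason for stratifying and then names age alone.
- **A reader might take the t-test to be the primary analysis.** The quoted tests cover the other endpoints. For primary VAS pain no test is named, which is a gap and not a decision.
- **A reader might say that a study objective goes unanswered.** No objective in section 2.0 compares age groups; age is a design rationale. Section 8.2 also tests for anaesthetic effect more often in the first 10 topical participants of each age group, which is some safeguard.
- **Section 9.2 is a summary.** Age could be added in the detailed plan, so the fair statement is that it is not specified here. Since departures from the summary must be documented, the summary is still the default.

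What remains is that the stratum and the reason for it have no counterpart in the stated analysis.

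**Conclusion.** The point holds as an omission worth correcting, not as an error that invalidates the trial. Section 9.2 specifies unadjusted tests for the non-primary endpoints, no test for the primary one, and no result by age group, although age is the named stratum and possible age differences are the reason for the two groups.

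The precision cost is modest and depends on the assumed age gap: the SE is about 4%, 10% and 20% too large at gaps of 1, 1.5 and 2 points with total SD 1.8, and not at all at zero. Power for the 1-point design effect is essentially unchanged. These figures assume comparison as randomised, equal age groups and exact 2:1 allocation within them.

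The larger cost is that an effect confined to one age group would be halved in the pooled result and not located. Estimates by age group are precise enough to be useful. The interaction is not precise enough for a null result to reassure.

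**What to change.** In section 9.2 or the detailed analysis plan:

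1. Name the primary analysis of VAS pain: a linear model with arm and age group, giving the adjusted difference and 95% CI. Site may be added for precision. If the block lists prove to be by site as well, site is a stratum and belongs in the model for that reason.
2. Analyse binary endpoints with a Mantel-Haenszel risk difference stratified by age group.
3. Report the arm difference with 95% CI separately for ages 10-15 and over 15, plus an arm-by-age interaction estimate labelled exploratory and low-powered.
4. Tabulate Phase I adverse events by age group as well as by site.

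In section 4.0, state whether the block lists are issued by age group only or by site and age group, for both phases.

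The cost is wording and a few extra tables. Age and site are already known for every participant, and neither the sample size nor the visit schedule changes.
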